#### Data Capture

Immediately after initial login, participant information is captured as per the table in the Multimedia Appendix 1. Data capture then occurs on both the presearch and postsearch answer screens, as listed in Table 1. All system interactions will also be captured including (1) overall time spent searching for and answering each question; (2) dwell times before first query, on the SERP screen, on the document viewing screen, and on the answer screen; (3) the participant’s search query terms and resulting SERP; (4) documents selected from the SERP; (5) evidence selected by the participant from the documents they are viewing; and (6) relevance ratings by the participant of the documents they view (essential, helpful, duplicate-essential, duplicate-helpful, and not helpful). Multimedia Appendix 3 itemizes the search interaction times and how these relate to the study timings. Although desirable, it is not possible to question the participant regarding the utility of each search system because the user is not made aware of which search system is in use for each task.

Anonymity of the data collected is maintained by (1) identifying users and all of their interactions with a random user identification within the data capture system, (2) having no participant identification information stored in the same system database, and (3) capturing only generic participant information (see Multimedia Appendix 1) that could not be used to identify an individual.

### Availability of Data and Material

The datasets generated and/or analyzed during this study as well as access to the software for the Taskiir search system are currently not publicly available because the study is still underway and therefore not complete.

At the completion of the study, the following research data will be made available on the University of Queensland’s publicly accessible eSpace data repository [36]:

Excel spreadsheet containing all data reported by the user (as specified in the *Data Capture* section above) by task including answers to all study questions and task responses. Overall task timings will also be provided here.mySQL database (anonymized) containing the raw data captured, including detailed user-task interaction timings, search terms, SERP results, SERP clicks, document selections, document relevance selections, and evidence selection text.Auxiliary Excel/text files containing summarized subsets of (2), as required for further research and analysis.

### Clinical Tasks

The criteria for task selection was that each task must (1) have answers able to be found in the literature, (2) be able to be answered with yes/no/conflicting information or a single-term/phrase response, (3) be credible to a practicing clinician, and (4) have nonobvious answers. Overall, 6 of the 16 clinical questions are those produced and used by Westbrook et al [16] and are reproduced here in Table 2. The tasks consist of real-life scenarios and a clinical question for each scenario. Westbrook et al derived the tasks using clinical experts and designed them to be clinically relevant and of mixed complexity. In addition, 4 questions are sourced from Hersh et al [18], which are also clinical questions and used for the same purposes as this study. Overall, 3 questions are modified from the text retrieval conference (TREC) 2015, clinical decision support (CDS) topic set [37]. These questions were provided with diagnoses, which our medical physician (DA, MBBS), modified into a question of a similar format to the other questions. Finally, our medical physician also devised a further 3 other clinical questions for the purposes of this test. Moreover, 2 general practitioners trialed all questions for suitability.

**Table 1 table1:** Data capture on the presearch and postsearch answer screens.

No	Data: purpose	Measurement	Presearch	Postsearch
1	Answer: Decision quality	Select (Yes/no/conflicting evidence/do not know) or type answer depending on the question	Yes	Yes
2	Confidence in answer: impact of the system on answer confidence	How confident are you in your answer? (1=no confidence, 2=a little confident, 3=moderately confident, 4=very confident, and 5=certain)	Yes	Yes
3	Perceived difficulty: relationship with time constraints and answer quality	How would you rate the difficulty of this clinical question? (presearch) and How would you rate the difficulty of the search for evidence for this task? (postsearch). (1=very easy, 2=easy, 3=neither easy nor difficult, 4=difficult, and 5=very difficult)	Yes	Yes
4	Perceived impact of time constraint on decision: relationship with decision quality and confidence	How would you rate the time you had available to make your decision? (1=not nearly enough time, 2=nearly enough time, 3=just enough time, 4=more than enough time, and 5=much more than enough time)	N/A	Yes
5	Perceived impact of time constraint on decision: relationship with decision quality and confidence	How would you rate the time you had available to collect evidence? (1=not nearly enough time, 2=nearly enough time, 3=just enough time, 4=more than enough time, and 5=much more than enough time)	N/A	Yes
6	Perceived impact of time constraint on participant’s stress level: relationship with decision quality and confidence	How much stress did you feel due to time pressure? (1=none, 2=a little, 3=a moderate amount, 4=a lot, and 5=more than a lot)	N/A	Yes

**Table 2 table2:** Task specifications including the full task scenario supplied to the participant as well as the relevant reference from the corpus that supports the answer.

Question	Source
Cytobrush Pap Smear: Is the Cytobrush superior to a spatula for obtaining cells for Pap smears, in terms of technical quality (eg, percentage of interpretable smears)? [18]	[38,39]^a^
Glue Ear: A mother brings her 15-month-old son who has been seen three times in the past year for glue ear. She has heard that this can lead to learning and developmental problems and thinks her child may need surgery. His hearing is normal. Does current evidence support the need for the insertion of tympanostomy tubes to avoid developmental problems in this child? [16]	[40]
Asthma Inhaler: What is the best delivery device for effective administration of inhaled medication to a 5-year-old child during a moderately severe acute asthma attack? [16]	[41]
Nicotine Replacement Therapy after heart attack: A patient staying in hospital had a myocardial infarction two days ago and is now threatening to sign himself out. You suspect this is due to nicotine withdrawal. The patient wishes to stop smoking and seeks your advice on whether he can start nicotine replacement therapy. Is nicotine replacement therapy appropriate for this patient? [16]	[42,43]
Glucosamine sulfate: A 58-year-old woman with long-standing pain of osteoarthritis in knees, hips, and hands asks about the benefits of glucosamine sulfate. Does existing evidence demonstrate that glucosamine has a disease modifying role in osteoarthritis? [16]	[44]
Brown snake: A man is bitten by a brown snake and is taken to the hospital emergency department. There is clear evidence of envenoming (poisonous effects of venom). The hospital has run out of brown snake antivenom, so the patient must be given polyvalent snake antivenom (which contains antivenom for all Australian snakes). Should epinephrine be given with the antivenom to prevent anaphylaxis? [16]	[45,46]
Osteomyelitis diabetic foot: What anaerobic microorganism is most commonly found in osteomyelitis associated with diabetic foot? [16]	[47]^a^
Ultrasound for Deep Vein Thrombosis (DVT): Is ultrasound the best diagnostic test available to exclude the presence of lower extremity deep vein thrombosis? [18]	[48,49]^a^
Protein-losing nephropathy: Does dietary protein effect the level of proteinuria in patients with diabetic (a type of protein-losing) nephropathy? [18]	[50,51]^a^
Bladder Cancer: Is there evidence of an association between petroleum product exposure and bladder cancer? [18]	[52]^a^
Loin pain: A 48-year-old man presents with severe right sided loin pain and is diagnosed with a 4 mm distal ureteric calculus. Has Tamsulosin been shown to increase the chances of the calculus passing?^b^	[53,54]^a^
Breast cancer: Is oestrogen receptor positivity a better prognostic factor than human epidermal growth factor receptor 2 (HER2) overexpression for patients with breast cancer?^b^	[55]^a^
Dementia: Are the clinical effects of Mematine, when used as a sole agent in the treatment of Alzheimer’s Dementia, greatest in the “mild” stage of the disease?^b^	[56]^a^
Paroxysmal nocturnal hemoglobinuria: Is flow cytometry the most accepted laboratory investigation to confirm a suspected diagnosis of Paroxysmal Nocturnal Hemoglobinuria? [AD modified TREC CDS 2015 [37], Q14].	[57,58]^a^
Anaemia: Is the efficacy and side effect profile of oral iron polymaltose and oral ferrous sulfate equivalent when used for the treatment of iron deficiency anaemia among children? [AD modified TREC CDS 2015 [37], Q27].	[59]^a^

^a^Answer provided by author, [name] (MBBS).

^b^Question derived by author, [name] (MBBS).

In Westbrook et al’s study, 6 sources of evidence were available to search by the clinicians; however, only medical literature was provided in this study, as this was the source of evidence under investigation. To ensure that at least 1 relevant document existed in the corpus for each task, our medical physician searched through the corpus, using the search system, to identify 1 or more relevant documents. The resulting relevant PubMed sources are listed for each question in Table 2. The answers are excluded in this protocol to avoid any chance of participants viewing the answers before completing the study. However, they will be provided together with the results data.

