**Figure 1 figure1:**
[figure not shown]
Process flow diagram of study shows both stages of the study. Stage 1 is untimed and the clinician has no access to any support resource. In stage 2, each question is timed and the participant is allocated a search engine to use for each question. If time runs out, the participant is brought directly to the task completion page.

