### Sample Size

The 2 largest and most similar studies [16,18], both commenced with a presearch correct answer rate of around 30% (29% and 32%) and a postsearch rate around 50% (50% and 46%). Using this as our basis, we wanted to be able to discriminate between the postsearch correct answer rate between each of the 3 time-constrained cohorts. Therefore, to derive the sample size, we estimated that the correct answer rates might vary evenly by 10 percentage points between each group, starting at no improvement. This creates 3 datasets with average correct answer rates of 30%, 40%, and 50% for the 3-, 6- and 9-min cohorts, respectively. Applying a 2-proportion statistical comparison (ie, a 2-sample, 2-sided equality) [66], between each pair of answer rates and setting statistical power to 90%, error rate to 5%, and equal sample sizes per cohort, the minimum sample size required is 514 per cohort, which equates to 32 people per cohort sitting 16 tasks or 96 people in total.

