### Statistical Analyses

To assess the impact of introducing the SML search system on clinical decision quality (RQ-1), each participant’s answer, both presearch and postsearch, will be coded to right (R) or wrong by comparing the participant’s answer with an expert judged assessment (gold answer) of each task. Samples for which (1) no evidence is captured and (2) no relevant documents are marked (either as essential or helpful), by the participant for their postsearch answer, will be discarded, as the value of the search system cannot be confirmed in these cases. Therefore, the decision quality is defined by the correct answer rate (number of right answers/total sample count (N)). A further detailed analysis will be performed of the collected evidence to identify tasks where the literature may contradict the gold answers. Where this occurs, the task answers will be reviewed by experts and overall correct rates adjusted.

To assess the significance of any change in the proportion of right or wrong answers, the McNemar test will be employed because it is a nonparametric test suited to a binary result, with samples taken at 2 points in time. Nonparametric is a better model to assume, given that the data distribution is unlikely to be regular because of the different medical groupings of participants. The sign test, which is also a nonparametric test, will be used to identify any significant changes to the correct rate. To assess any differences between the participant groups (nurses, doctors, and students), a Chi-square analysis will be performed. The participant’s confidence in their answers will be assessed presearch and postsearch to identify any significant changes relating to search intervention, also using chi-square analysis.

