To assess the impact of time constraints on clinical decision quality (RQ-2), the analyses above will be repeated with a breakdown by time constraint category, that is, 3, 6 and 9 min. In addition, an analysis of time-outs by constraint category will be conducted to assess the impact of time constraints on task completion. Time-outs are defined as samples where at the postsearch answer stage (1) the task timer reaches the constraint duration and (2) the participant provides no evidence to support their answer. It is assumed that in a time-out scenario, the participant was unable to complete the task. Significant differences by time-constraint category will be analyzed using the chi-square analysis. An analysis of variance (ANOVA) will be performed across confidence, difficulty, participant-perceived time impact assessments (impact of time on answer, evidence capture, and stress), and search behaviors, such as SERP dwell time, number of queries issued, number of documents opened, and the quantity of evidence items selected. To gain an understanding of the impact of providing a time constraint on the decision-making process, both the average time to search and the average proportion of available search time used will be evaluated and compared for the different task-timing samples. Tombros et al [67] used this proportional figure as a further gauge of participant stress and it can be compared with the reported stress by the participants.

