To assess the impact of search engine performance on clinical decision quality (RQ-3), a similar set of analyses will be performed as that for RQ-1, except broken down by search system (state-of-the-art and BM25). In addition, the same ANOVA methods employed for time-constraint categories in RQ-2 analysis will be performed. In addition, an ANOVA will be performed across system categories and system time constraints to identify cases where system performance effects may matter most. The impact of search engine performance on clinical decision time (RQ-3) will also be assessed by evaluating the postsearch task completion times for those tasks that were completed (ie, relevant documents and/or evidence identified). This is measured in 2 ways: (1) search time only and (2) search time plus time spent filling in the answer form. Differences in search times between the systems will be assessed using the chi-square analysis. Finally, a participant-derived performance assessment of the 2 systems can be constructed by building a graded query relevance (QREL) listing (standard format for representing relevance assessments in IR), by query, based on all participants’ relevance ratings. Using this QREL, a recomparison of the 2 systems can be evaluated and compared using the formal TREC evaluation results to provide better insight into any changes observed (or not) in the clinical decision and timing results for the 2 systems.

There are a number of potentially confounding factors within the experimentation. A covariant analysis (repeated measure ANOVA) will be performed on the task number, task at total duration point (for fatigue), and time transitions (eg, 3-min task to 6-min task and 3-min task to 9-min task).

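### The ANOVAs on difficulty and confidence should name the postsearch rating as outcome and use the presearch rating as a covariate; the two difficulty items ask different things

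*Protocol article*

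**What the plan says.** Table 1 (Methods, Clinical Tasks) lists what is captured on the two answer screens. Row 3 has one label and one purpose, "Perceived difficulty: relationship with time constraints and answer quality", and is marked as collected both before and after the search. The wording differs by stage: "difficulty of this clinical question? (presearch) and How would you rate the difficulty of the search for evidence for this task? (postsearch". Row 2, confidence, asks one and the same question at both points. Rows 4 to 6 (time for the decision, time for evidence, stress) are collected only after the search.

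The Figure 1 caption separates the exposures. Of the first stage it says "Stage 1 is untimed and the clinician has no access to any support resource"; of the second, "In stage 2, each question is timed and the participant is allocated a search engine to use for each question". Under Procedures, all 16 Stage 1 tasks come before Stage 2, and a task's limit is announced when that task starts in Stage 2.

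For RQ-2, Statistical Analyses states: "An analysis of variance (ANOVA) will be performed across confidence, difficulty, participant-perceived time impact assessments", followed by search behaviours, with time limit as the factor. For RQ-3, by search system, "the same ANOVA methods employed for time-constraint categories in RQ-2 analysis will be performed". The same section ends with a covariate analysis on task number, elapsed duration and time transitions; the presearch ratings are not among these. A comparison of ratings before and after search is stated for confidence: "The participant’s confidence in their answers will be assessed presearch and postsearch to identify any significant changes relating to search intervention". None is stated for difficulty.

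**The concern.** Two items that measure different things share one name, and the analysis text uses only that name. One asks how hard the clinical question is; the other asks how hard it was to find evidence. The first is given before the participant meets that task's limit or either search system, so neither can affect it. It can be a baseline but not an outcome for RQ-2 or RQ-3. The purpose given in row 3, so far as it concerns time limits, fits only the second item.

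Two things are at stake, both small. First, the analyst is left to choose which rating enters the ANOVA, and one available choice, a pre-to-post change in difficulty, would subtract one construct from another and have no clear meaning. Second, each answer comes with a pre-exposure rating by the same participant on the same task, for difficulty and for confidence, and the ANOVAs by limit and system do not use it. Adjusting for it would sharpen both comparisons without new data.

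**Working it through.** **1. The plan's own figure.** The article gives no figure for difficulty or confidence. Its sample size rests on the correct answer rate, with "average correct answer rates of 30%, 40%, and 50% for the 3-, 6- and 9-min cohorts, respectively". For 40% against 50%, two-sided 5% and 90% power, the unpooled formula gives (1.960 + 1.282)² × (0.40×0.60 + 0.50×0.50) / 0.10² = 514.9. The stated 514 therefore reproduces, but it does not bear on this point.

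**2. Which rating can respond to the exposure.**

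| Rating | When given | Limit or system in force? | Possible role in the ANOVAs |
|---|---|---|---|
| Question difficulty | Stage 1 | Neither | Baseline covariate |
| Presearch confidence | Stage 1 | Neither | Baseline covariate |
| Search difficulty | Stage 2, after search | Both | Outcome |
| Postsearch confidence | Stage 2, after search | Both | Outcome |

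**3. Precision gained by adjustment.** Inputs: n = 512 answers per limit (16 tasks × 32, from Task Order, System Rotation, and Task Timing). Assumed, not in the article: unit SD at each stage, a linear relation with correlation ρ between an answer's two ratings, and independent answers.

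- Unadjusted SE of a difference between two limits: √(2/512) = 0.0625.
- Adjusted SE: √(2(1 − ρ²)/512). At ρ = 0.3 this is √(2 × 0.91/512) = 0.0596.
- Relative reduction: 1 − √(1 − ρ²). It does not depend on n, so it applies equally to the comparison of systems.

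| Assumed ρ | √(1 − ρ²) | Fall in SE |
|---|---|---|
| 0.2 | 0.980 | 2% |
| 0.3 | 0.954 | 5% |
| 0.4 | 0.917 | 8% |
| 0.6 | 0.800 | 20% |

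**4. The same gain as power.** Assume also a true postsearch difference of 0.2 SD and ρ = 0.3. Unadjusted: 0.2/0.0625 = 3.20, power about 89%. Adjusted: 0.2/0.0596 ≈ 3.35, power about 92%. The gain is about 3 percentage points.

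**5. What the sum leaves out.** Each participant rates 16 tasks, so answers are clustered. If the model already carries task and participant effects, these absorb part of what the presearch rating explains, and the gain may be smaller than shown.

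**The case against.** A reader might infer that the ANOVA mixes the baseline with the outcome, because one label covers both. If the two ratings were averaged and the presearch one were unaffected, a postsearch effect would be halved; under the assumptions above power would be about 51%. If their difference were analysed, it would be about 77%. The documents do not support that inference. Nothing says the ratings are pooled, averaged or subtracted. Time limits and systems exist only in Stage 2, and every other variable listed in that ANOVA except confidence is collected only after the search. Where the authors want a before-and-after comparison of ratings, they say so, and they say it for confidence. The postsearch rating alone is therefore the natural reading, and the 51% and 77% price analyses that nobody has planned. Even if both ratings were used, halving would follow only from averaging or from stacking them under one main effect; separate ANOVAs would leave the postsearch estimate as it is.

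It can also be said that Table 1 prints both wordings and marks each with its stage, that naming the item is detail an article may leave to a fuller analysis plan, and that omitting a covariate is not an error. All of this stands. The missing name alone would not be worth raising. What is left is that the ANOVAs, as described, pass over a pre-exposure measurement that is already collected and is not among the covariates listed.

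**Conclusion.** A minor improvement, not a defect that threatens a conclusion. Row 3 of Table 1 joins two constructs under one label, the ANOVAs for RQ-2 and RQ-3 do not name the rating, and the presearch ratings of difficulty and confidence go unused in them. No bias or loss of power in the plan is shown.

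The benefit of adjustment is a standard error lower by 2% to 20% for correlations from 0.2 to 0.6. The article gives no correlation, effect size or SD for these ratings, so the range is illustrative. Because the two difficulty items differ in content, their correlation cannot be presumed high; the confidence item is identical at both stages. The correct answer rate, its tests and the sample size are unaffected.

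**What to change.** In Statistical Analyses, for the ANOVAs by time limit (RQ-2) and by search system (RQ-3):

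- name postsearch search difficulty and postsearch confidence as the outcomes;
- include the same answer's presearch rating as a covariate: question difficulty for the first, presearch confidence for the second;
- state that no pre-to-post change in difficulty will be reported, because the two items measure different things.

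In Table 1, give the two halves of row 3 separate names, such as question difficulty and search difficulty. The before-and-after comparison of confidence planned for RQ-1 can stay.

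The cost is wording only. Table 1 shows both ratings collected at both stages, and the article reports the study as still under way, so the choice could be fixed before results are seen.
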